#### Secondary outcomes

The secondary outcomes are impact of synbiotic consumption on the presence of enteropathogens and parasites in stools, biomarkers of gut health in stool and blood, biomarkers of systemic inflammation, growth hormones, faecal microbiota composition and epigenetics markers. Stool samples collected at 1, 6 and 24 months will be analysed using multiple methods including bacterial culture, quantitative PCR and ELISA for the following:

Enteropathogens: *Salmonella*, *Shigella* and pathogenic *Escherichia coli*.Enteroparasites: helminths (*Ascaris lumbricoides*, *Ancylostoma duodenale*, *Necator americanus*, *Trichuris trichiura* and *Strongyloides stercoralis*) and protozoans (*Giardia lamblia*, *Cryptosporidia parvum*/*hominis* and *Entamoeba histolytica*/*dispar*).Intestinal inflammation: myeloperoxidase.Intestinal permeability: α_1_-antitrypsin.Maturation of gut microbiota, assessed using Illumina-based 16S rRNA gene amplicon sequencing.

Blood samples collected at 6 and 24 months will be analysed for

Chronic inflammation: alpha-1-acid glycoprotein.Acute inflammation: C reactive protein.Gut mucosal integrity: intestinal fatty acid binding protein.Growth hormones: insulin-like growth factor (IGF)-1 and its carrier protein IGF-binding protein 3.

Saliva samples collected within 1 month of birth and at 18–24 months will be analysed for epigenetic status including markers of gut and general health and growth.

Procedures for the transportation, storage and handling of the aforementioned biological samples will be detailed in other protocols of the supplement (for blood and stool samples, see protocol titled ‘Assessment of the role of gut health in childhood stunting in a multi-site, longitudinal study in India, Indonesia, and Senegal: a UKRI GCRF Action Against Stunting Hub protocol paper’, and for saliva samples, see Epigenetics protocols and methods).

Infants who develop adverse events that may be due to the study intervention will be identified by parents/carers contacting study staff or at follow-up visits. If appropriate, participants will be referred to the hospital for evaluation and treatment according to local guidelines. In the case of a serious adverse event (SAE), subjects will be referred to an appropriate health facility for management. All SAEs will be reported to the in-country principal investigator or an assigned representative within 24 hours of the research staff becoming aware of it. The information reported will include the nature of the event, date of onset, severity, corrective therapies given, outcome and causality (ie, unrelated, unlikely, possible, probably and definitely). The responsible study clinician will assign the causality of the event. SAEs that are unexpected and are at least ‘possibly related’ to the study intervention will require expedited reporting within 24 hours of the in-country principal investigator or assigned representative becoming aware of it. This will be a maximum of 48 hours after the event occurred or the study team was made aware of the event (including the 24 hours required for the field staff to report to the principal investigator/representative). Additional information will be sent within 14 additional days (full SAE report) if the reaction had not resolved at the time of email notification.

### Sample size determination

The sample size calculation is based on observing a clinically meaningful improvement in linear growth in the intervention arm. In the WASH Benefits study in Kenya, the control group (n=1431) at median age of 12 months (range 2–18 months) had a mean LAZ of −1.13 (SD=1.13).^5^ To observe a 25% improvement in LAZ at age 12 months (ie, LAZ=−0.8475, SD=1.13) with 80% power, α=0.05 and with 1:2 group allocation would require 189 infants in the intervention group and 378 in the control group. We plan to allow for 20% loss to follow-up by recruiting 236 to the intervention group and 472 to the control arm. Based on previous studies, we consider that this number of infants will also be sufficient to observe meaningful differences in biomarkers between the study arms.^8 10 12 20^

### Data management and statistical analysis

#### Data and sample management and governance

Data and sample management will follow procedures established by the AASH. This includes a data sharing strategy that will build on the guiding principles for scientific management and stewardship and Concordat on Open Research Data to ensure equitable access to data. Data will be transmitted via secure file transfer protocols between Senegal and hub partners in the UK, Indonesia and India. A data monitoring and evaluation committee (DMEC), a trial steering committee (TSC), research ethics committees of Liverpool School of Tropical Medicine (LSTM) and London School of Hygiene and Tropical Medicine, and Senegal National Ethics Committee for Scientific Research will oversee the conduct of the trial. The trial sponsor, LSTM, will review the trial at initiation, during the study and at trial close-out with additional monitoring visits as required. The trial may be stopped or suspended by the sponsor at any stage due to any arising safety concerns or following the recommendation of the DMEC and/or TSC.

### Statistical analysis

Analysis of the primary and secondary endpoints will be based on intention to treat. Mean/median values of biomarkers, the proportion of infants with abnormal biomarker concentrations, gut colonisation with enteropathogens and the proportion of infants/children with episodes of illnesses will be compared in the two arms at 1, 6 and 24 months. Additional analysis of the primary and secondary endpoints will also be presented according to adherence to synbiotic administration. Data will be analysed using generalised linear models with treatment as the only predictor, generating the estimates of treatment effects and their 95% CIs. For outcomes with repeated measurements, the linear model will have a binomial distribution and logit link function for binary outcomes and a normal distribution and identify link function for continuous outcomes. Mean differences between the two treatment arms together with 95% CIs will be derived from the appropriate linear model. Missing data will be treated as missing completely, and no imputation of primary or secondary endpoints will be made. Adjustment for covariates and inclusion of interaction terms will be performed as appropriate. More details on statistical analysis methods using secondary variables will be described in other papers in the supplement.

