**Methods and analysis:**

An individually randomised, two-arm, open-label, controlled trial will be conducted in Kaffrine District, Senegal. Infants will be recruited at birth and randomised to either receive a synbiotic containing two *Bifidobacterium* strains and one *Lactobacillus* strain, or no intervention, during the first 6 months of life. The impact of the intervention will be evaluated primarily by comparing length-for-age z-score at 12 months of age in infants in the intervention and control arms of the trial. Secondary outcome variables include biomarkers of intestinal inflammation, intestinal integrity and permeability, gut microbiota profiles, presence of enteropathogens, systemic inflammation, growth hormones, epigenetic status and episodes of illness during follow-up to age 24 months.

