## Methods and analysis

### Trial design

Senegal Synbiotic (SENGSYN) is an individually randomised, two-arm, open-label, controlled trial. The protocol for this trial has been developed in accordance with the Standard Protocol Items: Recommendations for Interventional Trials guideline. The trial is part of the research conducted within the UK Research and Innovation Global Challenges Research Fund (UKRI GCRF) Action Against Stunting Hub (AASH) (https://actionagainststunting.org/), an interdisciplinary research consortium investigating the precursors of child stunting to inform programmes and policies to reduce the global burden of this condition. Infants born to women recruited during pregnancy in Kaffrine, Senegal in the AASH observational study will be assessed for eligibility and recruited to participate in the SENGSYN trial.

Recruited infants will be randomised to receive either a daily supplement of a synbiotic in the first 10 days of enrolment and then weekly up to 6 months of age, or no intervention, with the children followed up to 24 months of age. Detailed anthropometry will be conducted at birth and months 3, 6, 12, 18 and 24; stool samples will be collected at 1, 6 and 24 months; and blood samples will be collected at 6 and 24 months. Assessments of morbidity and breast feeding are conducted weekly up to 24 months of age (table 1).

**Table 1 T1:** Schedule of enrolment, intervention and assessments

	Study period										
	Enrolment/allocation	Post allocation									Close-out
Time point	Birth	1 month	2 months	3 months	4 months	5 months	6 months	9 months	12 months	18 months	24 months
Enrolment											
Eligibility screen	X										
Informed consent	X										
Random allocation	X										
Intervention											
Intervention arm		Synbiotic daily for 10 days then weekly until 6 months									
Control arm		Routine care									
Assessments											
Weekly morbidity diary		X	X	X	X	X	X	X	X	X	X
Body weight, breast feeding	X	X	X	X	X	X	X	X	X	X	X
Other anthropometry		X		X			X	X	X	X	X
Stool pathogens/microbiota/ biomarkers		X					X				X
Blood biomarkers							X				X
Epigenetic status in saliva		X									X

The trial follows the Standard Protocol Items: Recommendations for Interventional Trials protocol.

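### Illness is recorded weekly to 24 months, but the only comparison the article states is a proportion at 1, 6 and 24 months with no window; an episode rate would use the diary better

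*Protocol article*

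**What the plan says.** Three places in the protocol article bear on illness.

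- **Outcome.** The abstract's methods paragraph lists among the secondary outcomes "episodes of illness during follow-up to age 24 months". The Introduction also names illness episodes among the effects to be assessed. The detailed list under Secondary outcomes does not include them.
- **Collection.** Under Trial design, "Assessments of morbidity and breast feeding are conducted weekly up to 24 months of age". Table 1 shows a weekly morbidity diary throughout.
- **Analysis.** Under Statistical analysis, "the proportion of infants/children with episodes of illnesses will be compared in the two arms at 1, 6 and 24 months". No look-back period is given. For outcomes measured repeatedly, the model has "a binomial distribution and logit link function for binary outcomes and a normal distribution and identify link function for continuous outcomes". No count, rate or recurrent-event model is named. The section closes by deferring further detail: "More details on statistical analysis methods using secondary variables will be described in other papers in the supplement".

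No illness incidence, expected illness effect or illness power is stated. The trial is sized on length-for-age z-score (LAZ) alone.

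**The concern.** The outcome is recurrent and followed continuously, while the stated summary is binary at three ages. Those ages are the stool-sampling times. They suit the biomarkers named in the same sentence, but have no special meaning for a weekly diary.

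Without a window, the proportion has at least two plain readings, and neither measures episodes over follow-up well. If it means ill at any time up to that age, a child with one episode counts the same as a child with ten, time at risk plays no part, and both arms drift towards 100% when illness is common. If it means ill at or shortly before the visit, most of the diary goes unused.

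At stake is precision on a secondary outcome that the Introduction makes prominent: it motivates the trial with a large trial in which a synbiotic reduced infections in newborns. An insensitive summary makes a null illness result hard to interpret.

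**Working it through.** **1. The plan's own figure.** Sample size determination gives a control group that "had a mean LAZ of −1.13 (SD=1.13") and aims "To observe a 25% improvement in LAZ at age 12 months", a difference of 0.25 × 1.13 = 0.2825. With 80% power, two-sided α = 0.05 (two-sided is assumed) and 1:2 allocation:

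n(intervention) = (1 + 1/2) × [(1.960 + 0.842) × 1.13/0.2825]² = 188.4, so 189, and 2 × 189 = 378 controls. Dividing by 0.8 gives 236.25 and 472.5, against the stated 236 and 472. The figure reproduces. I use 189 v 378 below.

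**2. Assumptions for illness.** None of these is in the documents: control rate 3 episodes per child-year; negative binomial counts with variance μ + kμ² and k = 0.5; rate ratio 0.80.

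**3. Formulas.** With μ = rate × years:
- P(at least one episode) = 1 − (1 + kμ)^(−1/k).
- Power of the proportion = Φ[(|p1 − p2| − 1.96·s0)/s1], with s0 the pooled and s1 the unpooled standard error.
- Power of the rate = Φ[|ln RR|/SE − 1.96], with SE² = (1/μ1 + k)/189 + (1/μ2 + k)/378. Here |ln 0.8| = 0.2231.

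**4. To 6 months (the dosing period).** μ = 1.2 v 1.5.
- Proportion: 60.9% v 67.3%, difference 0.0641, s0 = 0.0424, s1 = 0.0429; power Φ(−0.44) = 33%.
- Rate: SE² = 1.3333/189 + 1.1667/378 = 0.01014, SE = 0.1007; power Φ(2.22 − 1.96) = 60%.

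**5. To 24 months, if the effect lasts throughout.** μ = 4.8 v 6.0.
- Proportion: 1 − 3.4⁻² = 91.3% v 1 − 4⁻² = 93.8%, difference 0.0240, s0 = 0.0228, s1 = 0.0239; power Φ(−0.87) = 19%.
- Rate: SE² = 0.7083/189 + 0.6667/378 = 0.00551, SE = 0.0742; power Φ(3.01 − 1.96) = 85%.

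**6. Other control rates**, to 24 months, k = 0.5, same rate ratio:

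| Episodes per child-year | Controls ever ill | Power, proportion | Power, rate |
|---|---|---|---|
| 1 | 75% | 32% | 67% |
| 2 | 89% | 25% | 80% |
| 3 | 94% | 19% | 85% |
| 4 | 96% | 16% | 88% |
| 6 | 98% | 12% | 90% |

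Over rates of 2–4 and k of 0.3–1.0, 24-month power is 14–29% for the proportion and 60–96% for the rate.

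**7. Short look-back.** Past-week illness at three visits uses 3 of about 2 × 52 = 104 weekly records, or 2.9%. Power per time point is about 4–10% over 0.5–6 episodes per child-year.

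**8. Where the gain disappears.**
- One month at 3 per child-year (μ = 0.20 v 0.25): 17% for the proportion, 20% for the rate.
- A rare illness, 0.10 control episodes per child in the window (μ = 0.08 v 0.10): 10% and 11%.

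**9. Effect confined to 0–6 months.** The 24-month means become 1.2 + 4.5 = 5.7 v 6.0. Then |ln RR| = 0.0513, SE = 0.0731 and z = 0.70. Counting both tails, rate power is about 11%, and the proportion has about 6%.

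**The case against.** The strongest reply is that this is a condensed article. It defers secondary-variable methods to other papers, and one sentence covers biomarkers, colonisation and illness together. Windows and additional rate analyses may be set out elsewhere. That stands against any claim that illness will be analysed in no other way. It does not remove the point, because added detail supplements the comparison stated here and does not withdraw it.

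Further objections hold and limit the size:

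- **A third reading exists.** The repeated-measures logit model could be fitted to each week's ill or not-ill record, which would use the whole diary. So a reader might infer that the plan must either saturate or discard most records, but with the window unstated neither is established.
- **Saturation depends on incidence.** It needs about 2 or more episodes per child-year. At 0.5, only 50–63% of controls are ever ill by 24 months (k from 1 to 0).
- **The proportion is not always weak.** For a 30% reduction and k = 0 it reaches about 90% power in some windows, though the rate then has about 100%.
- **The 24-month contrast needs a lasting effect.** Dosing stops at 6 months, and the Discussion expects weaker effects once complementary food starts.

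A reader might also infer that a child lost early is counted as free of illness, so that unequal loss biases the comparison. The article does not say so. Its rule of no imputation suggests that such a child is left out, and it does not predict unequal loss.

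**Conclusion.** The point holds as one of efficiency and definition for a secondary outcome. The article states a binary illness comparison with no window for weekly recurrent data, and a rate from the same records matches the named outcome better.

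Under the assumptions in the working, the gain is from about 33% to 60% power over 0–6 months, and from about 19% to 85% over 24 months only if a 20% reduction persists throughout. For a 20% reduction, the proportion did not exceed about 53% power in any window over 0.5–6 episodes per child-year and k of 0–1. The rate did at least as well throughout, with almost no gain for rare illnesses or the first month.

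It does not follow that a real effect would probably be missed because of the proportion, or that a rate makes the trial well powered for illness. Even the rate has only 60% in the dosing period, and about 11% over 24 months if the effect ends with dosing. Incidence, dispersion and effect are all assumed. The primary LAZ analysis and the sample size are untouched.

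**What to change.** Make the main illness analysis episodes per observed child-time from the weekly diary: negative binomial regression with the log of observed child-time as offset, and terms for arm and clinic (the randomisation stratum). Use 0–6 months, the dosing period, as the main window and report 6–24 months separately. A child lost early then contributes the weeks observed. Keep the proportion ever ill as descriptive, with its window stated.

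The cost is small. The data are already collected, so the change is to analysis-plan wording. A rule for when a new episode begins must be written, and there is slightly more analysis work.

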### Study setting

The trial is based in Kaffrine District, Senegal. The total population is 257 696 inhabitants. The population of children under 23 month is 17 780, and the prevalence of low birth weight (BW) is 17%. Data from 2015 indicated a prevalence of stunted children under five of 26.8%.^19^ The district has 28 health posts or clinics and 32 health huts administered by the Kaffrine Health Centre. The AASH will recruit participants in seven clinics, and women participating in the AASH study will be targeted for the recruitment of their newborns in the SENGSYN study. More details on the study setting will be provided in the supplement paper on the overview of study design, data collection and management procedures of the AASH.

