### Participants

Pregnant women recruited into the AASH observational study will be given an information sheet about this synbiotic trial at recruitment (online supplemental file 1). The women will be further approached by study staff at health facilities or in their homes within 3 days of delivery to determine whether their newborn meets the inclusion criteria and if she/he does, to obtain informed consent for participating in the SENGSYN trial (see online supplemental file 2)

10.1136/bmjpo-2022-001629.supp1Supplementary data

10.1136/bmjpo-2022-001629.supp2Supplementary data

Inclusion criteria are

Singleton newborn.BW or current weight (if BW not known) of ≥2000 g.Healthy infant who is breast fed and has taken at least one breastfeed well.Age 1–3 days.

Exclusion criteria are

Multiple birth (eg, twins, triplets, etc).Presence of any acute illness in the newborn (eg, fever and receiving treatment with antibiotics).Congenital abnormality that might be life-threatening or might impair growth.Infant with potential contraindication to synbiotic (eg, suspected immune suppression and cardiac abnormality).Mother unlikely to stay in study area for the duration of the trial.Any health- or study staff concerns regarding safety to participate in the trial.

Infants of women known to be HIV positive and without known immunosuppression are eligible to participate in the trial.

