### Randomisation and allocation

The trial statistician will prepare a computer-generated random allocation sequence using R-coding, with blocks of random size stratified by clinic, allocating newborns to one of two study arms:

Arm 1: Labinic synbiotic every day for 10 days and then weekly to age 6 months.Arm 2: control group, usual care with no supplement.

Participants (infants) will be allocated at a ratio of 1:2 in the intervention and control arms, respectively. The allocation sequence will be held by an independent pharmacist in Senegal who will prepare sequentially numbered, sealed, opaque envelopes according to the random allocation sequence. The random allocation sequence will be concealed from all other members of the research team including staff allocating newborns to the trial arms and laboratory staff analysing the biological samples. Each envelope will be opened sequentially following recruitment of each newborn and will contain a card indicating the trial arm. The trial arm will then be linked to the infant’s unique AASH identification number. Mothers/carers who decline for their infant to participate in the SENGSYN study will continue in the AASH observational cohort.

Following participant allocation, study staff will assist the mother/carer in administering the first dose of the synbiotic to infants in the intervention arm.

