#### Primary outcome

The primary outcome of the trial is linear growth at age 12 months assessed by LAZ. Regularly calibrated equipment for anthropometry will include a Model 876 SECA/infant scale, UNICEF stadiometer/infantometer, Lufkin WP601 measuring tape and Holtain skinfold calliper. Measurements will be conducted in duplicate with a third measurement taken if the first two measurements do not agree within a specified amount. Weight will be recorded to the nearest 100 g and height, length, mid-upper arm circumference, head circumference, triceps and subscapular skinfolds, and knee-to-heel length to the nearest 0.1 cm. Measurements will be used to determine z-scores using the WHO growth standards for LAZ, weight-for-length (WLZ), triceps-for-age and subscapular-for-age. Children will be classified as stunted or wasted if their LAZ or WLZ is <−2 SDs, respectively.

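### The stated treatment-only model leaves out the clinic stratum and the infant's weight at enrolment, so it gives up some precision, though the planned 80% power does not depend on them

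*Protocol article*

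**What the plan says.** The primary endpoint is a single continuous measure: "The primary outcome of the trial is linear growth at age 12 months assessed by LAZ" (Primary outcome). For the analysis, the article states: "Data will be analysed using generalised linear models with treatment as the only predictor" (Statistical analysis). Later in the same paragraph it adds: "Adjustment for covariates and inclusion of interaction terms will be performed as appropriate". No covariate is named there.

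On the design side, the allocation sequence is built "with blocks of random size stratified by clinic" (Randomisation and allocation), and "The AASH will recruit participants in seven clinics" (Study setting). Allocation is 1:2, intervention to control.

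On baseline size, eligibility requires "BW or current weight (if BW not known) of ≥2000 g" (Participants), so a weight is known for every infant before allocation. For length, the Trial design text says: "Detailed anthropometry will be conducted at birth and months 3, 6, 12, 18 and 24". Table 1 in that section marks body weight at birth, but the row for the other anthropometric measures is first marked at 1 month.

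**The concern.** Stratifying by clinic balances the arms within each clinic, so differences between clinics largely drop out of the treatment contrast. A model with treatment alone still counts those differences as residual noise. Whenever clinics differ in LAZ, its standard error is larger than the true sampling variability of the estimate. The design has paid for balance that the analysis does not use.

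Baseline size raises a separate issue of efficiency. If size at birth or enrolment predicts 12-month LAZ, putting it in the model removes explained variance and narrows the interval. The weight is already collected.

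This is a comment on a model the article states, not on detail it leaves out. At stake is precision on the primary comparison that would cost no infants and no visits.

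**Working it through.** **Inputs**

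- From Sample size determination: control mean LAZ −1.13, SD 1.13, target −0.8475, 80% power, α = 0.05, 189 intervention and 378 control evaluable. Difference: −0.8475 − (−1.13) = 0.2825.
- From Study setting and Randomisation and allocation: seven clinics, stratified blocks, 1:2.
- Not in the document, so assumed: the share *s* of LAZ variance lying between clinics (2% and 5%, with 10% as an outer case), and the correlation *r* of the baseline size measure with 12-month LAZ (0.3 to 0.5, with lower values shown).

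**1. The plan's own figure**

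n(intervention) = 2.8016² × (1.13/0.2825)² × (1 + 1/2) = 7.849 × 16 × 1.5 = 188.4, so 189, with 378 controls. This matches the article as an unadjusted, two-sided comparison.

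- SE = 1.13 × √(1/189 + 1/378) = 0.1007
- 95% CI half-width = 1.96 × 0.1007 = 0.197
- Power = Φ(0.2825/0.1007 − 1.96) = Φ(2.806 − 1.96) = 80.1%

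**2. Leaving out clinic**

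Under stratified allocation the true variance of the contrast is about (1 − s) times the variance that the treatment-only model estimates.

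- True α = 2[1 − Φ(1.96/√(1 − s))]
- Power with clinic in the model = Φ(2.806/√(1 − s) − 1.96)
- Actual power of the treatment-only test = Φ((2.806 − 1.96)/√(1 − s))

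| s (assumed) | True α, treatment only | Actual power, treatment only | Power with clinic |
|---|---|---|---|
| 2% | 0.048 | 80.4% | 80.9% |
| 5% | 0.044 | 80.7% | 82.1% |
| 10% | 0.039 | 81.4% | 84.1% |

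At 2% to 5%, clinic adds 0.8 to 2.0 points over the nominal 80.1%. Measured against the actual power of the treatment-only test, it adds about 0.5 to 1.4 points. The error in α is on the conservative side.

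**3. Leaving out baseline size**

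Residual SD = 1.13 × √(1 − r²). Half-width and power then follow as in step 1.

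| r (assumed) | r² | Half-width | Power |
|---|---|---|---|
| 0 | 0 | 0.197 | 80.1% |
| 0.14 | 0.02 | 0.195 | 80.9% |
| 0.22 | 0.05 | 0.192 | 82.1% |
| 0.3 | 0.09 | 0.188 | 83.7% |
| 0.4 | 0.16 | 0.181 | 86.5% |
| 0.5 | 0.25 | 0.171 | 90.0% |

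For r of 0.3 to 0.5 the interval narrows by about 5% (0.188/0.197 = 0.954) to 13% (0.171/0.197 = 0.868).

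**4. Simulation check**

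The set-up was seven equal clinics of 81 infants (567 in all), 1:2 blocks of three, clinic share 2% or 5%, r of 0.3, 0.4 or 0.5, and 3,000 runs per setting.

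- Power: 79.7% to 81.4% for treatment only; 83.4% to 91.4% with clinic and baseline size.
- Half-width: 0.198 for treatment only; 0.187 to 0.167 adjusted.
- Null rejection by the treatment-only test: 0.051 to 0.054 at a 2% share and 0.040 to 0.046 at 5%. The Monte Carlo standard error is √(0.05 × 0.95/3000) = 0.004, so the small conservatism expected at 2% cannot be seen above the noise, while that at 5% shows.

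**5. Which baseline measure exists before the first dose**

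Weight does, because eligibility depends on it and is settled before allocation. Length is not assured: the Trial design text places detailed anthropometry at birth, while Table 1 first marks it at 1 month. The first dose follows allocation, so a 1-month length is measured after treatment has begun and cannot serve as a baseline covariate.

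**The case against.** The strongest reply is that the stated analysis does what the trial was sized for. The sample size reproduces as an unadjusted comparison with 80% power, and an unadjusted difference in means is unbiased under randomisation. The one factor certainly omitted from the design, clinic, has a small effect that errs on the safe side. All of this stands. A reader might infer that the trial is underpowered or that its type I error is inflated, and the document supports neither.

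A second reply is that the gain from baseline size is assumed throughout. This also stands. The article gives no correlation and no clinic variance share. The assured covariate is weight, which mixes birth and current weights, and nothing in the document shows where in the assumed range it would fall. It would be tempting to treat birth LAZ as available at no cost and to quote power near 94% (which needs r = 0.6). Table 1 does not support the first, and no figure in the article supports the second.

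A third reply concerns the sentence on adjusting for covariates. A reader might infer that it contradicts the treatment-only model, creates two rival primary estimates, and lets the adjusted model be chosen after open-label data are seen. The document does not establish this. The paragraph can be read as an unadjusted main analysis with adjustment as further work, and naming and ranking covariates is commonly left to a statistical analysis plan, which is not shown.

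What these replies do not remove is that the article fixes a model without the factor used to stratify its own randomisation.

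**Conclusion.** The point holds as a matter of efficiency. The stated model omits the clinic stratum and a baseline size measure that is already collected. With clinic shares of 2% to 5%, the cost is a mildly conservative test (α about 0.048 to 0.044) and 1 to 2 points of power. With a baseline correlation of 0.3 to 0.5, the forgone gain is larger: power of about 84% to 90% against 80%, and a half-width of about 0.188 to 0.171 against 0.197. Both ranges are assumptions. If neither clinic nor baseline size predicts LAZ, almost nothing is lost. The existing analysis remains valid and meets its planned power, so the change is worth making but the trial does not stand or fall on it.

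**What to change.** - State the primary analysis of 12-month LAZ as a linear model with treatment, clinic and one named pre-dose size measure. Use birth or enrolment weight, and say which is taken when both exist.
- Use birth LAZ instead only if the Trial design text and Table 1 are reconciled and length is confirmed as measured before the first dose in all infants. Do not use the 1-month measurement as baseline.
- Include clinic in the secondary-outcome models. For binary outcomes on the logit scale, note that the odds ratio is then conditional on clinic.
- Keep the treatment-only estimate as a supporting analysis, and label any other covariate adjustment as exploratory.

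The cost is analysis wording only: no extra infants and, with weight as the covariate, no new data. The sample size can stay as it is.

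### The model stated for repeated secondary outcomes (treatment as sole predictor, plus a distribution and link) does not handle within-child correlation if visits are fitted jointly, and cannot give the by-visit comparisons the same section promises

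*Protocol article*

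**What the plan says.** All of the model text is in the protocol article, under Statistical analysis.

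- Predictors: "Data will be analysed using generalised linear models with treatment as the only predictor".
- Repeated outcomes: "For outcomes with repeated measurements, the linear model will have a binomial distribution and logit link function for binary outcomes", followed by a normal distribution with identity link for continuous outcomes. Nothing else in the section concerns repetition.
- Timing: biomarker levels, abnormal-biomarker proportions, enteropathogen colonisation and the proportion of children with illness "will be compared in the two arms at 1, 6 and 24 months".
- Flexibility: "Adjustment for covariates and inclusion of interaction terms will be performed as appropriate".
- Deferral: "More details on statistical analysis methods using secondary variables will be described in other papers in the supplement".

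The Trial design section shows which data are repeated: "stool samples will be collected at 1, 6 and 24 months", and "blood samples will be collected at 6 and 24 months". Dosing ends at 6 months of age. The primary outcome is a single length-for-age z-score (LAZ) at 12 months.

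**The concern.** The section sets out to cover repeated measurements, but a distribution and a link do not deal with repetition, and the stated predictor set leaves out visit. An ordinary generalised linear model fitted to all visits together treats two or three results from one child as results from different children. The comparison is between children, so positive within-child correlation then makes the standard error of the arm effect too small, other things equal.

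The same joint model returns one arm effect across all ages. It cannot produce a contrast at each of 1, 6 and 24 months, and it combines the 1- and 6-month visits (during or at the end of dosing) with a visit 18 months after dosing stops. An effect confined to the supplementation period would be diluted.

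At stake are the confidence intervals and tests for the stool and blood outcomes, which carry the trial's evidence on mechanism.

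**Working it through.** **1. The plan's own figure, and whether it is touched.** Inputs from Sample size determination: SD 1.13, difference 0.25 × 1.13 = 0.2825, 80% power, α = 0.05 (two-sided taken), allocation 1:2.

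Intervention n = (1 + 1/2) × (1.960 + 0.842)² × (1.13/0.2825)² = 1.5 × 7.849 × 16 = 188.4, so 189, with 378 controls. With 20% loss, 189/0.8 = 236.25 and 378/0.8 = 472.5, against 236 and 472 stated. The figures reproduce. They rest on one LAZ value per child, so the repeated-measures question does not enter.

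**2. Joint fit with correlation ignored.** Inputs: m = 3 stool visits and m = 2 blood visits (Trial design). The within-child correlation ρ is not in the document; I assume an exchangeable structure with ρ from 0.1 to 0.5.

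- Design effect: DE = 1 + (m − 1)ρ
- Model-based SE ÷ true SE = 1/√DE
- Actual two-sided error at nominal 5% = 2 × [1 − Φ(1.96/√DE)]

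| Outcome | ρ | DE | SE ratio | Actual error |
|---|---|---|---|---|
| Stool, m = 3 | 0.1 | 1.2 | 0.91 | 7.4% |
| | 0.3 | 1.6 | 0.79 | 12.1% |
| | 0.5 | 2.0 | 0.71 | 16.6% |
| Blood, m = 2 | 0.1 | 1.1 | 0.95 | 6.2% |
| | 0.3 | 1.3 | 0.88 | 8.6% |
| | 0.5 | 1.5 | 0.82 | 11.0% |

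Simulation with 189 and 378 children (5,000 runs each) gave 7.6%, 12.2% and 15.7% for three visits and 5.7%, 8.8% and 11.4% for two. Working with one mean per child, or with one visit alone, gave 4.4% to 5.4%.

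**3. Effect of also omitting visit.** For a continuous outcome, leaving visit out puts the variance V of the visit means into the residual. With within-visit variance 1, the ratio of true to model-based variance becomes DE/(1 + V). Both sets of visit means below are assumptions, with m = 3.

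| Visit means (SD) | V | ρ | DE/(1 + V) | Error, formula | Error, simulated |
|---|---|---|---|---|---|
| 0, −0.5, −1 | 0.167 | 0.1 | 1.03 | 5.3% | 5.4% |
| | | 0.3 | 1.37 | 9.4% | 9.1% |
| | | 0.5 | 1.71 | 13.4% | 14.6% |
| 0, −1, −2 | 0.667 | 0.1 | 0.72 | 2.1% | 1.9% |
| | | 0.3 | 0.96 | 4.5% | 4.2% |
| | | 0.5 | 1.20 | 7.4% | 7.6% |

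The error can therefore fall on either side of 5%.

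**4. Mixing of periods.** As an illustration, take a true effect of 0.25 SD at 1 and 6 months and none at 24 months. With equal numbers at each visit, the pooled estimate is (0.25 + 0.25 + 0)/3 = 0.17 SD.

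**5. The two readings side by side.** If visits are modelled jointly, a treatment-only model cannot deliver the contrasts at 1, 6 and 24 months. If each visit is analysed alone, a treatment-only model is valid, but the repeated-measurements sentence then says nothing about repetition. The section does not say which is meant.

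**The case against.** The strongest reply is that the article nowhere says visits will be pooled or records treated as independent. The sentence on comparing arms at 1, 6 and 24 months reads naturally as one comparison per visit. On that reading each child contributes one value, standard errors are correct and nothing is averaged. The repeated-measurements sentence would then merely give the distribution and link for outcomes collected more than once. A condensed article may leave the correlation structure to an analysis plan, covariates and interactions are allowed, and further detail on secondary outcomes is deferred to other papers.

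Much of this stands, and it is why the point is conditional on a joint fit. A reader might infer that on- and off-treatment effects will be averaged and that standard errors will be too small. The documents do not support that as a statement of fact: the by-visit sentence points the other way, and step 3 shows that the direction of error is not fixed even under pooling.

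A reader might also infer far larger distortions, by treating the weekly illness records ("Assessments of morbidity and breast feeding are conducted weekly up to 24 months of age") or serial LAZ values as independent rows. No such analysis is planned. Illness is to be compared as a proportion of children at the stated ages, and the primary outcome uses LAZ at 12 months only.

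What the reply does not remove is that the section positively states a predictor set without visit and assigns repeated outcomes a specification that does not address repetition. The allowance for covariates and interactions names no visit term, and covariates alone do not generally remove within-child correlation. A promise of more detail elsewhere does not withdraw the model stated here.

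**Conclusion.** The point holds for secondary outcomes with repeated measurements, on condition that visits are fitted jointly as written. In that case the model ignores within-child correlation, gives no contrast at each visit, and mixes the dosing period with a visit 18 months later. For assumed ρ of 0.1 to 0.5 and no shift in visit means, actual error at nominal 5% is about 7% to 17% for three stool visits and 6% to 11% for two blood visits. For continuous outcomes with large visit shifts it may be near or below 5%, so the proper description is an uncontrolled error rate. The values of ρ and the visit shifts are assumptions; the document gives neither.

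If each visit is analysed alone, there is no error to correct beyond unclear wording. The primary analysis and the sample size are unaffected under either reading. I rate this as a correction that should be made, below the level of one that must be made before the trial's main conclusion can be trusted.

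**What to change.** Replace the repeated-measurements sentence with one of two statements.

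- **Joint model.** A mixed model, or GEE with robust standard errors, clustered on child, with arm, visit and arm-by-visit terms. Report the arm contrast at each visit: a mean difference for continuous outcomes, and an odds ratio or marginal risk difference for binary ones. Restrict the treatment-only wording to outcomes measured once.
- **Separate visits.** State that each visit is analysed on its own with a treatment-only model, and delete the repeated-measurements sentence. Keep the distribution and link as general text, and name the effect measure for binary outcomes, since a logit model does not give the mean differences that the section mentions.

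The cost is a few lines of text and, for the joint model, slightly more code. No change to recruitment, visits or sample size is needed. Where a pooled fit would have understated the standard errors, the intervals will be wider.
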